## 1. Study Summary

This comprehensive retrospective cohort study aims to redefine the optimal prognostic threshold for minimal residual disease (MRD) detection in pediatric acute myeloid leukemia (AML) using data from the TARGET-AML initiative. The conventional MRD positivity threshold of ≥0.1% by multiparametric flow cytometry (MFC) will be compared against a proposed lower threshold of ≥0.05% to evaluate its superiority in risk stratification and prognostic accuracy. The study population comprises 1,205 pediatric AML patients with complete MFC-MRD data following induction chemotherapy courses. Primary endpoints include event-free survival (EFS) analysis using advanced statistical methods including Kaplan-Meier survival curves, Cox proportional hazards models, receiver operating characteristic (ROC) curves, and net reclassification improvement (NRI) analysis. The study aims to provide evidence-based recommendations for refining MRD monitoring standards in pediatric AML clinical practice.

## 2. Research Background and Scientific Rationale

Pediatric acute myeloid leukemia represents a heterogeneous group of hematologic malignancies characterized by clonal proliferation of myeloid precursors with impaired differentiation. Despite significant advancements in risk-adapted therapy approaches, including allogeneic hematopoietic stem cell transplantation for high-risk patients, relapse remains the predominant cause of treatment failure, with 5-year event-free survival rates plateauing at approximately 50-60% in contemporary clinical trials. Minimal residual disease monitoring has emerged as a critical component of modern risk stratification in acute leukemias. Among various MRD detection methodologies, multiparametric flow cytometry-based MRD assessment offers the advantage of rapid turnaround time, widespread availability, and applicability to nearly all patients regardless of genetic markers. The conventionally accepted threshold of 0.1% for defining MRD positivity has demonstrated prognostic utility across multiple studies, yet evolving technological capabilities in flow cytometry warrant reevaluation of this standard. Recent evidence suggests that lower levels of residual disease, previously classified as MRD-negative by the 0.1% threshold, may still harbor significant prognostic implications. Technological advancements now enable reliable detection of leukemic cells at levels as low as 0.01%, raising important questions about the optimal threshold for clinical decision-making. This study addresses a critical evidence gap by systematically evaluating a lower MRD threshold in a large, well-annotated pediatric AML cohort.

## 3. Research Objectives and Hypotheses

### 3.1 Primary Objectives

1. To determine the optimal MRD threshold for predicting 5-year event-free survival following Induction Course 1 and Course 2 chemotherapy using ROC curve analysis.
2. To compare the prognostic discrimination capacity of the traditional 0.1% MRD threshold versus a proposed 0.05% threshold through Kaplan-Meier survival analysis and hazard ratio calculations.
3. To quantify the improvement in risk classification accuracy using net reclassification improvement (NRI) analysis when applying the lower MRD threshold.

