### 3.3 Research Hypotheses

- **Primary Hypothesis**: An MRD threshold of 0.05% provides superior prognostic discrimination compared to the conventional 0.1% threshold for predicting 5-year EFS in pediatric AML.
- **Secondary Hypothesis**: The 0.05% threshold demonstrates consistent prognostic performance across all genetic risk categories and offers significant net reclassification improvement.

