### 4.5 Study Schema

Patient Identification (N=1,205)

↓

Inclusion/Exclusion Criteria Application

↓

Data Extraction and Validation

↓

Stratification by MRD Thresholds (0.1% vs 0.05%)

↓

Primary Analysis: EFS Comparison

↓

Secondary Analyses: Subgroup, NRI, Multivariate

↓

Results Interpretation and Validation

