### 7.2 Secondary Analyses

**Cox Regression**: Univariate and multivariate Cox proportional hazards models will assess the association between MRD thresholds and EFS, adjusting for relevant covariates. **Net Reclassification Improvement**: Categorical NRI will quantify improvement in risk prediction using the novel threshold. **Subgroup Analysis**: Consistency of the MRD threshold will be evaluated within predefined genetic risk categories.

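### NRI and hazard ratios are ranked primary in some sections and secondary in others, and no analysis in 7.1 is stated as the comparison of 0.05% with 0.1%

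*Protocol*

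**What the plan says.** **NRI.** Protocol 3.1 makes it the third primary objective: "To quantify the improvement in risk classification accuracy using net reclassification improvement (NRI) analysis when applying the lower MRD threshold". The Study Summary opens a sentence with "Primary endpoints include event-free survival (EFS) analysis using advanced statistical methods" and ends its list of methods with "Cox proportional hazards models, receiver operating characteristic (ROC) curves, and net reclassification improvement (NRI) analysis". Section 3.3 places NRI in the secondary hypothesis, under which the 0.05% threshold "demonstrates consistent prognostic performance across all genetic risk categories and offers significant net reclassification improvement". The schema in 4.5 has "Secondary Analyses: Subgroup, NRI, Multivariate". Section 7.2, headed as secondary analyses, has "Categorical NRI will quantify improvement in risk prediction using the novel threshold".

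**Hazard ratios.** Primary objective 2 compares the 0.1% threshold with a 0.05% "threshold through Kaplan-Meier survival analysis and hazard ratio calculations". Section 7.2 covers both univariate and multivariate Cox models. Secondary objective 2 in 3.2 concerns the multivariate model only.

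**What is left as primary.** The schema gives "Primary Analysis: EFS Comparison". Section 7.1 has two items: Kaplan-Meier curves with a log-rank test by MRD status at both thresholds, and ROC curves with Youden's index to find the best cut-off for 5-year EFS status. The primary hypothesis in 3.3 claims superior prognostic discrimination for 0.05% and names no measure, course or test.

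**The concern.** The study asks whether one cut-off is better than another, and the data already exist. The main protection against choosing a favourable result is a statement, made in advance, of which result answers the question. Here the ranking of the analyses is the only guide, and it conflicts between sections. Two things follow.

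- Read literally, one primary objective and part of another have no primary analysis.
- An investigator could call a favourable NRI primary by citing 3.1, or call an unfavourable one secondary by citing 3.3, 4.5 and 7.2. The same choice exists for the unadjusted hazard ratio between 3.1 and 7.2.

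If the measures always pointed the same way, this would be a matter of labels. The question is whether they can diverge.

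**Working it through.** **Step 1: rank of each measure by section.**

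| Section | NRI | Unadjusted hazard ratio | Adjusted Cox model |
|---|---|---|---|
| 1 Study Summary | in the primary-endpoints sentence | Cox models in the same sentence, type not given | as left |
| 3.1 | primary (objective 3) | primary (objective 2, adjustment not stated) | not named |
| 3.2 | not named | not named | secondary |
| 3.3 | secondary hypothesis | not named | not named |
| 4.5 | secondary | not named | secondary |
| 7.1 | absent | absent | absent |
| 7.2 | secondary | secondary | secondary |

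NRI is primary in two places and secondary in three. For the unadjusted hazard ratio the conflict is between 3.1 (with the Summary) and 7.2 alone. The adjusted model is secondary wherever it is named as such.

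**Step 2: does 7.1 settle the question anyway?** The log-rank test compares MRD-positive with MRD-negative patients at each cut-off. Both tests can be significant without showing that either cut-off is better. Youden's index picks a cut-off, and no test, margin or rule sets 0.05% against 0.1%. The sample size section (5.3) does not help. It gives a hazard ratio of 2.0, 80% power and α=0.05, but no number of events, so there is no figure to reproduce. Assuming a two-sided test and equal groups, the Schoenfeld formula gives (1.960 + 0.842)² / (0.25 × (ln 2)²) = 7.85 / 0.120, or 66 events. If 40% to 50% of 1,205 patients have events (assumed from the 50-60% 5-year EFS in section 2), that is about 482 to 602 events. Power then exceeds 99% even with 10% MRD-positive. This describes positive against negative patients, not one cut-off against the other.

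**Step 3: can the measures disagree?** The protocol gives no distribution of MRD levels, so these inputs are assumptions:

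- 25% of patients at 0.1% or above, with 70% having events;
- 8% between 0.05% and 0.1%, with event risk p varied;
- 67% below 0.05%, with 38% having events.

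Lowering the cut-off moves only the middle band, and moves all of it to positive. Hence

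NRI = (share of events in the band) − (share of non-events in the band).

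This is also the change in sensitivity plus the change in specificity, so the two-category NRI equals the difference in Youden's index between the cut-offs. The hazard ratio is approximated under proportional hazards as ln(1 − risk in positives) / ln(1 − risk in negatives). Censoring is ignored.

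For p = 50%:

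- Total event share = 0.175 + 0.040 + 0.2546 = 0.4696; non-events 0.5304.
- NRI = 0.040/0.4696 − 0.040/0.5304 = 0.0852 − 0.0754 = +0.010.
- Cut-off 0.1%: risks 0.70 and 0.2946/0.75 = 0.3928; HR = 1.204/0.499 = 2.41.
- Cut-off 0.05%: risks 0.215/0.33 = 0.6515 and 0.38; HR = 1.054/0.478 = 2.20.

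| p | NRI | HR at 0.1% | HR at 0.05% | NRI favours | HR favours |
|---|---|---|---|---|---|
| 45% | −0.005 | 2.46 | 2.13 | 0.1% | 0.1% |
| 50% | +0.010 | 2.41 | 2.20 | 0.05% | 0.1% |
| 55% | +0.025 | 2.37 | 2.28 | 0.05% | 0.1% |
| 60% | +0.039 | 2.33 | 2.36 | 0.05% | 0.05% |

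NRI turns positive once the band's risk exceeds the pooled risk of the other patients, here 0.4296/0.92 = 46.7%. The hazard ratio does not favour 0.05% until somewhere between 55% and 60%. Between those points the two measures give opposite answers.

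**The case against.** **The Summary is weak evidence.** Its sentence can be read as naming EFS as the endpoint and then listing methods, without ranking them. That is fair, but the conflict stands without it: 3.1 against 3.3, 4.5 and 7.2 for NRI, and 3.1 against 7.2 for hazard ratios.

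**The detail may belong in a separate SAP.** A testing hierarchy often does, and its absence here is not the complaint. The complaint is that the protocol ranks the same measure in two ways, and its own section 7 is titled as the statistical analysis plan.

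**All the analyses will be run whatever their label.** True, but the label decides which one answers the primary hypothesis, and step 3 shows that this can matter.

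**Stronger readings to avoid.** A reader might infer that hazard ratios are also made secondary in the schema and the hypotheses. They are not. The schema names only the multivariate analysis, in line with secondary objective 2. The hypotheses do not mention hazard ratios, and the primary hypothesis uses the idea of prognostic discrimination that objective 2 ties to Kaplan-Meier and hazard ratios.

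A reader might also multiply three primary objectives by two induction courses and compute a false-positive rate for six tests. The protocol does not support that. Only objective 1 names both courses, objective 1 estimates a cut-off, objective 3 quantifies a change, and no superiority test at 0.05 is specified for either. The measures also overlap.

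**Conclusion.** The inconsistency is real and can be checked by reading. NRI is a primary objective in 3.1 but secondary in 3.3, 4.5 and 7.2. Hazard ratios are in primary objective 2, yet every Cox model is secondary in 7.2. The primary analysis section leaves objective 3 and part of objective 2 unserved and states no comparison of the two cut-offs.

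The consequence is that the conclusion can depend on the section read. The illustration shows that this is possible (NRI +0.010 with the hazard ratio falling from 2.41 to 2.20), not that it is likely. It rests on assumed group shares and event risks, proportional hazards and no censoring, and compares point estimates only. At 45% or 60% risk in the middle band the measures agree.

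It does not follow that NRI and hazard ratios should be made secondary. That would remove the labelling conflict but leave in 7.1 only analyses that are not stated as comparisons of 0.05% with 0.1%. The point should be corrected before analysis; it does not invalidate the design.

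**What to change.** 1. Give NRI one rank and the unadjusted hazard ratio one rank, and carry these through sections 1, 3.1, 3.3, 4.5 and 7. Promoting or demoting NRI would each resolve the conflict; the choice is the sponsor's.
2. Before analysis, name in 7.1 one measure that directly compares the 0.05% and 0.1% cut-offs, at one named induction course, as the result that decides the primary hypothesis. One example is the difference in Youden's index for 5-year EFS with a confidence interval. The estimate should allow for censoring, since 5.1 admits survivors with 36 months of follow-up. As this difference equals the two-category NRI, the two should be reported as one result and not as separate pieces of evidence.
3. Label the remaining measures supportive, and state that they cannot replace the deciding result.

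The cost is protocol wording only; no new data are needed. The downside is that fewer results can be headlined as primary.

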### 3.2 Secondary Objectives

1. To validate the consistency of the proposed 0.05% MRD threshold across established genetic risk subgroups (low-risk, standard-risk, high-risk).
2. To establish the independent prognostic value of the novel MRD threshold through multivariate Cox regression analysis adjusting for known clinical and molecular variables.
3. To assess the clinical utility of the lower threshold in guiding treatment decisions, particularly regarding transplantation candidacy.

### 3.3 Research Hypotheses

- **Primary Hypothesis**: An MRD threshold of 0.05% provides superior prognostic discrimination compared to the conventional 0.1% threshold for predicting 5-year EFS in pediatric AML.
- **Secondary Hypothesis**: The 0.05% threshold demonstrates consistent prognostic performance across all genetic risk categories and offers significant net reclassification improvement.

## 4. Study Design

### 4.1 Study Type

Retrospective cohort study utilizing existing data from the TARGET-AML database.

### 4.2 Data Source

The Therapeutically Applicable Research to Generate Effective Treatments (TARGET) initiative database, version dated April 28, 2021, containing comprehensive clinical and laboratory data from pediatric AML patients treated between September 1996 and December 2016.

### 4.3 Study Period

Data collection period: September 1996 to December 2016 Analysis period: January 2025 to June 2025

### 4.4 Study Setting

Multicenter collaborative analysis with primary data management and statistical analysis conducted at Sun Yat-sen Memorial Hospital, Sun Yat-sen University.

### 4.5 Study Schema

Patient Identification (N=1,205)

↓

Inclusion/Exclusion Criteria Application

↓

Data Extraction and Validation

↓

Stratification by MRD Thresholds (0.1% vs 0.05%)

↓

Primary Analysis: EFS Comparison

↓

Secondary Analyses: Subgroup, NRI, Multivariate

↓

Results Interpretation and Validation

## 5. Study Population

### 5.1 Inclusion Criteria

- Pediatric patients (<18 years at diagnosis) with newly diagnosed de novo AML (non-M3 subtype)
- Availability of MFC-MRD data measured after completion of Induction Course 1 and/or Course 2
- Treatment according to one of the specified protocols: AAML03P1, AAML0531, or AAML1031
- Complete baseline clinical and molecular characterization data
- Minimum follow-up duration of 36 months for surviving patients

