### 5.2 Exclusion Criteria

- Acute promyelocytic leukemia (M3 AML) patients
- Patients with incomplete MRD data or key prognostic variables
- Secondary AML or therapy-related AML cases
- Patients with insufficient follow-up data

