### 6.3 Variable Definitions

- **Event-free survival (EFS)**: Time from diagnosis to first event (induction failure, relapse, secondary malignancy, or death from any cause)
- **MRD positivity**: Defined using two thresholds: traditional (≥0.1%) and novel (≥0.05%)
- **Complete remission**: <5% blasts in morphologically normal bone marrow with recovery of peripheral counts
- **Genetic risk groups**:
  - Low risk: inv(16)/t(16;16) or t(8;21)
  - High risk: monosomy 7 or del(5q)
  - Standard risk: All other cases with adequate cytogenetic data

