## 7. Statistical Analysis Plan

### 7.1 Primary Analysis

**Survival Analysis**: Kaplan-Meier method will be used to estimate EFS distributions stratified by MRD status at both thresholds. The log-rank test will compare survival curves.

**ROC Analysis**: Receiver operating characteristic curves will determine the optimal MRD threshold for predicting 5-year EFS status using Youden's index.

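### The 36-month follow-up minimum applies only to survivors, so the cohort is selected on part of its own endpoint and Kaplan-Meier EFS is biased downward, probably by a small amount

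*Protocol*

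**What the plan says.** Section 5.1 of the protocol lists among the inclusion criteria "Minimum follow-up duration of 36 months for surviving patients". No minimum applies to patients who died. Section 5.2 adds the exclusion "Patients with insufficient follow-up data" without saying what counts as insufficient or whether it applies to deceased patients.

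Section 6.3 defines EFS as "Time from diagnosis to first event (induction failure, relapse, secondary malignancy, or death from any cause"). Section 7.1 states that the "Kaplan-Meier method will be used to estimate EFS distributions stratified by MRD status at both thresholds", with a log-rank test, and section 7.2 adds Cox models. Section 7.1 also states: "Receiver operating characteristic curves will determine the optimal MRD threshold for predicting 5-year EFS status using Youden's index".

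On timing, section 4.2 describes "pediatric AML patients treated between September 1996 and December 2016" and a database "version dated April 28, 2021". Section 4.3 gives a data collection period that ends in December 2016. No section gives a follow-up cut-off date or the extent of loss to follow-up. None of the sensitivity analyses in section 7.3 (multiple imputation, a landmark, competing risks) brings back patients whom the follow-up rule made ineligible.

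**The concern.** Whether a patient enters the cohort depends on whether that patient later died, and death is part of the primary endpoint. Someone who died at month 4 is in. Someone alive and last seen at month 30 is out, although those 30 months belong in the risk sets. Someone who relapsed at month 12 and was last seen alive at month 30 is also out, although the EFS event was observed.

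The criterion has no evident purpose that would offset this. Kaplan-Meier, log-rank and Cox analyses need no minimum follow-up, and 36 months does not establish the 5-year status that the ROC analysis uses.

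At stake are the absolute EFS estimates reported for each MRD group at each threshold and, if loss to follow-up differs by MRD status, the difference between the groups.

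**Working it through.** The protocol gives no figure for the effect of this rule, so there is none to reproduce. The check derives the direction, then the size under stated assumptions.

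**Direction.** Let C be the follow-up a patient would have if death did not intervene, and assume it is independent of outcome. Let L be the share with C below 36 months, x the share of the cohort that the rule removes, and S(t) the true EFS.

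- All patients with C of 36 months or more are kept (share 1 − L). They are an unbiased sample.
- Patients with C below 36 months are kept only if they died before C (share L − x). Each of them has an EFS event before month 36.
- No retained patient is censored event-free before month 36, so Kaplan-Meier EFS at 36 months is the simple proportion (1 − L)·S(36)/(1 − x).
- After month 36 only patients with C of 36 months or more remain at risk, so the hazard is correct from there on.

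Hence the 5-year estimate under the rule is S(60) × (1 − L)/(1 − x). Since x cannot exceed L, the factor is at most 1. It equals 1 when L = 0.

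**Size when short follow-up is only loss to follow-up.** Section 2 gives "5-year event-free survival rates plateauing at approximately 50-60% in contemporary clinical trials". The other inputs are assumptions: most events early (median 10 months among those who fail), 20% of first events are deaths, 35% of relapsed patients are salvaged, the others die at a median of 12 months after relapse, and loss is non-informative. The excluded share x comes from simulating the rule as written, including removal of relapsed survivors.

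| True 5-year EFS | Lost by month 36 (L) | Excluded (x) | EFS under the rule | Bias (points) |
|---|---|---|---|---|
| 50% | 5% | 4.3% | 50 × 0.950/0.957 = 49.6% | −0.4 |
| 50% | 10% | 8.5% | 50 × 0.900/0.915 = 49.2% | −0.8 |
| 50% | 20% | 17.1% | 50 × 0.800/0.829 = 48.3% | −1.7 |
| 60% | 10% | 8.8% | 60 × 0.900/0.912 = 59.2% | −0.8 |
| 60% | 20% | 17.7% | 60 × 0.800/0.823 = 58.3% | −1.7 |

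For a cohort with true 5-year EFS of 56.6% (62.7% in MRD-negative and 40.8% in MRD-positive patients) and constant annual loss r, L = 1 − (1 − r)³:

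| Annual loss | L | x | EFS under the rule | Bias (points) |
|---|---|---|---|---|
| 1% | 3.0% | 2.6% | 56.6 × 0.970/0.974 = 56.4% | −0.2 |
| 3% | 8.7% | 7.6% | 56.6 × 0.913/0.924 = 55.9% | −0.7 |
| 5% | 14.3% | 12.5% | 56.6 × 0.857/0.875 = 55.4% | −1.2 |
| 8% | 22.1% | 19.4% | 56.6 × 0.779/0.806 = 54.7% | −1.9 |

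Keeping everyone and censoring at last contact returns the true value in each scenario. About 17% of the excluded patients had an observed EFS event.

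**Size if follow-up also ends early for administrative reasons.** From the end of December 2016 to 28 April 2021 is about 52 months, so if follow-up runs to the version date only patients lost to follow-up are affected. If it ended earlier, more survivors fall under 36 months. With follow-up limits spread evenly over 24 to 120, 12 to 84 or 6 to 66 months, the rule removes about 10%, 27–28% or 41–43% of patients and the bias is about −1.6, −4.4 or −7.3 points.

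**Effect on the contrast between MRD groups.** Within a group the bias is −S(60)·(L − x)/(1 − x), and L − x is roughly proportional to the group's event fraction. With equal loss the bias therefore scales roughly with S(1 − S): 0.627 × 0.373 = 0.234 in MRD-negative and 0.408 × 0.592 = 0.242 in MRD-positive patients. Both groups shift by nearly the same amount and the gap stays. In simulation with equal loss of 8% a year, the hazard ratio moved only from 1.81 to 1.80 at the 0.1% cut and from 1.78 to 1.77 at the 0.05% cut, and Youden's index was unchanged to three decimals. With unequal loss the gap moves. Loss of 8% a year in MRD-negative and 3% in MRD-positive patients narrows it from 21.6 to 20.5 points; 2% and 5% widens it from 21.7 to 22.4.

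**The case against.** The strongest reply is that the study compares two cut-offs in the same patients, so a small shift in absolute EFS does not touch its question. With equal loss in both MRD groups this stands: hazard ratios and Youden's index barely change. It does not cover the absolute EFS curves that will be reported, or unequal loss.

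A second reply is that the number affected may be negligible. That also stands as a limit. The documents do not give it, and the annual loss rates above are assumed.

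A third is that plain censoring is unbiased only if loss is unrelated to prognosis. That is true, but the survivor-only rule does not cure informative loss.

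Three stronger readings are tempting and are not supported:

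- A reader might put the bias at −0.5 to −3.9 points for the same annual loss rates. Those figures come from removing only event-free patients. The criterion also removes relapsed survivors, which takes out events and roughly halves the bias.
- A reader might infer that the rule raises the 5-year event fraction used for ROC and NRI. Event-free patients lost before 36 months have no known 5-year status with or without the rule. Among patients with known status the rule removes only events, so the fraction falls (for example from 49.6% to 48.8% at 3% annual loss). It would rise only with a censoring-adjusted estimate, or if censored patients were counted as non-events. The protocol specifies neither.
- A reader might take the 52-month interval as proof that only patients lost to follow-up are removed. The April 2021 date is a database version, not a follow-up cut-off, and section 4.3 ends data collection in December 2016.

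**Conclusion.** The point holds. Section 5.1 conditions eligibility on survival, section 6.3 makes death part of EFS, and nothing elsewhere in the protocol offsets this. The direction, downward, follows from the rule itself, provided follow-up length is independent of outcome. The size rests on assumptions: about 0.2 to 1.9 points of 5-year EFS at 1% to 8% annual loss, under 1 point if up to 10% are lost by month 36, zero if no survivor has under 36 months, and several points if follow-up stopped well before April 2021. The comparison of MRD groups is little affected unless loss differs by MRD status. This is a defect that should be fixed before analysis. It does not invalidate the comparison of 0.05% with 0.1%.

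**What to change.** Delete the survivor-only 36-month criterion from section 5.1 and the undefined follow-up exclusion from section 5.2. Include every otherwise eligible patient, censor EFS at last contact, and state the follow-up cut-off date. Report median follow-up by reverse Kaplan-Meier, overall and by treatment protocol. If maturity of follow-up is a concern, restrict by diagnosis date, applied identically to living and deceased patients.

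If the criterion is nevertheless kept, report how many patients it removes in each MRD group and add a sensitivity analysis without it.

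The cost is two deleted criteria and a slightly shorter average follow-up. No new data are needed.
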